## Abstract

**Background:**

Sub-threshold depression is common, impairs functioning, and increases the risk of developing major depression. Although psychological treatments have been investigated for sub-threshold depression, they are costly. A less costly alternative could be an educational health promotion campaign about effective self-help for depression symptoms. The aim of the study is to test the efficacy of a low-cost email-based mental health promotion campaign in changing self-help behaviour and preventing more severe depression in adults with sub-threshold depression.

**Methods/Design:**

The project is a randomised controlled trial of an automated preventive email-intervention aimed at people with sub-threshold depression. Adults aged 18+ with sub-threshold depression (as measured with the Patient Health Questionnaire-9), who are not already receiving professional treatment for depression, are eligible for admission to the study. Internet users will sign up via the study website http://www.moodmemos.com and be randomly allocated to receive emails twice weekly for six weeks containing either self-help coping advice or general information about depression as a control. Outcomes will be assessed at the start, midpoint, and end of the intervention, as well as six months later. Outcomes assessed include symptoms, incidence of major depression, psychological distress, social and occupational functioning, coping strategies, and coping self-efficacy. The primary hypothesis is that the Mood Memo emails containing coping strategies will reduce depression symptoms and be better at preventing major depression than the control emails that contain general information about depression.

**Discussion:**

Promotion of actions an individual can take to prevent physical disease is a technique often used in public health. This study applies this approach to mental health, and explores whether a low-cost, easily disseminated email-based campaign can improve self-help coping behaviour and prevent depression in adults with sub-threshold depression.

**Trial Registration:**

Australia and New Zealand Clinical Trials Register (ANZCTR): ACTRN12609000925246

## Background

Evidence suggests that depressive disorders exist on a continuum, rather than as qualitatively distinct syndromes [1]. Depressive symptoms that fall short of diagnostic criteria (variously termed sub-threshold, sub-clinical, sub-syndromal, mild, or minor depression) are prevalent [2], cause significant functional impairment [1,3], have considerable economic costs [4], and increase the risk of developing major depressive disorder [5]. Sub-threshold depression is of major public health significance because of its substantial population disease burden which, in turn, arises from its high prevalence combined with significant disability to the individual.

Treatment of sub-threshold depression with psychological interventions (e.g., cognitive behaviour therapy) is moderately effective [6]. However, addressing the problem in formal health-care systems may not be an ideal solution, as health care resources are already stretched treating those with depressive disorders, yet there remain many with depressive disorders who do not receive treatment [7]. An alternative approach is self-help that can be used by individuals without the need for professional guidance. Self-help strategies, such as exercise or taking time off work, are liked by the public and are often used by those with depressive symptoms [8]. However, some commonly used strategies may be ineffective or even harmful (e.g., drinking alcohol). [9].

Our previous research has identified a set of self-help coping strategies judged to be effective by an international group of depression experts. These strategies include becoming more physically active, improving sleep habits, and doing activities that give a sense of achievement [10]. Health promotion campaigns encouraging the public to use effective self-help strategies for depression symptoms could be a cost-effective solution to reducing population disease burden [11]. This would be analogous to physical health promotional campaigns advocating behaviour change to reduce risk of disease (e.g., heart disease). This approach is rarely used in the mental health field. It could be applied to individuals with sub-threshold depression, with the aim of reducing symptoms and also to reduce the risk for the development of major depression. Intervening early could also improve functioning and prevent progression to other undesirable outcomes such as harmful substance use.

The internet is an excellent medium for the promotion of self-help messages, as it has significant population penetration, can cost-effectively reach large numbers of people, and is a frequently-used source of information about mental health problems [12]. In contrast to media traditionally used to promote health messages, internet technology potentially affords greater personalisation and interactivity, which may lead to greater persuasion and increase the likelihood that an individual will change their coping strategies [13]. Furthermore, website-based interventions for depression have proved effective [14], and health messages sent via email have improved health behaviours, such as improving diet and physical activity levels [15].

### Aim

The aim of the study is to determine the effectiveness of a mental health promotion campaign encouraging the use of a range of self-help coping strategies for sub-threshold depression, which have been identified by experts in the field. The study will evaluate the feasibility of the internet as a means of intervention, and will evaluate the impact of the intervention on depression symptom severity and incidence rates of major depression.

## Methods/Design

### Design

The project is a randomised controlled trial of an automated preventive intervention for adult internet users with elevated levels of depressive symptoms that do not meet diagnostic criteria for major depression (sub-threshold depression). The period of intervention is 6 weeks. Assessments are undertaken at baseline, 3-weeks, 6-weeks, and at 6-months after the end of the end of the intervention. The study was approved by the University of Melbourne Human Research Ethics Committee (HREC 0931313), and is registered with the Australian New Zealand Clinical Trials Registry (ACTRN12609000925246).

### Participants

Participants will be admitted to the trial if they are aged 18 or over; have sub-threshold symptoms of depression; are not receiving treatment for depression from a professional (e.g., doctor, counsellor, psychologist), not including maintenance antidepressant medication for 6 months or more; are a resident of Australia, New Zealand, UK, Ireland, Canada or the USA; and have access to the internet at least weekly. Sub-threshold symptoms are defined as two to four symptoms of depression [16] experienced most of the time for two or more weeks, which have affected work, home, or social functioning. Participants will be recruited to the project website http://www.moodmemos.com from internet-based sources, such as paid advertising on Google, Yahoo, and Facebook, and promotion through websites, forums, blogs, and email groups related to depression, mental health, research, or depression risk-factors. It is planned that the project website homepage will be archived at the end of the trial using a service such as WebCite[17].

### Sample size

The effect size of the intervention is anticipated to be small, given that indicated prevention of depression has a small effect size of d = 0.23 [18]. Similarly, unsupported internet-based treatment of depression has a small effect size of d = 0.25 [14]. A power analysis indicated that a sample of 393 per condition would give 80% power to detect a small effect size (0.2 standard deviations between conditions) on a continuous outcome measure assuming a correlation of 0.5 between pre- and post-test scores [19]. Because depression internet trials have a median dropout rate of 33% [20], a total sample of 1200 participants will be aimed for.

### Trial procedure

The administration of the intervention is fully automated using PHP 5 and a MySQL 5 database. Participants who visit the project website and give their informed consent to participate are screened for sub-threshold depression. They will be categorised into one of three depression status groups based on their results:

1) Sub-threshold depression: 2 to 4 symptoms of depression present for more than half the days or nearly every day (except for suicidality, which is counted as a symptom if present for only several days or more), for 2 weeks or more, with significant impact on functioning

2) Probable major depression: 5 or more symptoms of depression present for more than half the days or nearly every day (except for suicidality, which is counted as a symptom if present for only several days or more), for 2 weeks or more, with significant impact on functioning

3) Non-depressed: not meeting criteria for sub-threshold or major depression, i.e. too few symptoms, too short duration, little or no impact on functioning.

Depression symptoms are defined as the nine symptoms in criterion A of DSM-IV Major Depressive Episode [16] assessed with the PHQ-9 (see Assessment below). Depression status is scored by the system and trial eligibility is determined immediately, based on admission criteria. Those whose results indicate major depression or non-depressed will be given feedback on their score and informed that they are not eligible to participate. In addition, those with major depression will be encouraged to seek professional help and will be directed to a section on the website that provides contact details of organisations that provide help or support for mental disorders, broken down by country.

Participants with a positive screen for sub-threshold depression will be assessed to see whether they meet further inclusion criteria (see admission criteria above) and asked to provide their name or a pseudonym and an email address. An email will be sent to the address provided, which will contain a link to the baseline questionnaire package. Once the baseline assessment is completed, participants will be randomised to the active group or control group using the mt_rand() PHP script. Immediately following randomisation, participants will be sent their first Mood Memos email.

Each participant will receive emails twice a week for six weeks. Emails will be automatically generated by the system and personalised with relevant information (e.g., name) from the database. One email reminder per assessment point will be sent to those participants who have not completed assessments one week after being sent the email inviting completion of assessment. Participants who do not complete assessments will continue to receive the intervention, and may rejoin assessment at later timepoints.

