### Depression

The depression module of the Patient Health Questionnaire (PHQ-9) [45] will be used to assess depression. It is a self-rated questionnaire that makes probable diagnoses of mental disorders based on DSM-IV criteria [46]. The PHQ-9 consists of items covering the 9 symptoms of criterion A for a DSM-IV diagnosis of Major Depressive Episode [16]. Each item is rated in terms of its frequency over the last two weeks, from 0 (not at all) to 3 (nearly every day). Its structure means it can be used both to make probable diagnoses of major depression and sub-threshold depression, as well as to measure the severity of symptoms (0 to 27). An additional question asks about the impact of the symptoms on the person's functioning, analogous to criterion C of DSM-IV Major Depressive Episode [16]. The PHQ-9 has excellent reliability assessed by internal-consistency [45,47,48], adequate test-retest reliability [45,49], excellent criterion validity [50], and is sensitive to change [47,51]. It has been used in studies of internet treatment of depression [52], to assess rates of sub-threshold depression in the community [53], and to measure treatment of sub-threshold depression in primary care [54].

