### Statistical analysis

Primary effectiveness analyses will be undertaken on an intention-to-treat basis. Any participants who were randomised but who withdraw from the study, or who take up alternative treatments, will be included in the analysis as randomised. Continuous outcomes (PHQ-9 scores, K10 scores, WSAS scores) will be evaluated using mixed models for repeated measures (MMRM) [68]. This method of analysis will be utilised because of its ability to include participants with missing data under the assumption that observations are missing at random (MAR). The inclusion of an additional measurement occasion halfway through the intervention should increase the tenability of the MAR assumption. *A priori *contrasts will compare change from baseline at the primary endpoint (post-intervention) and at 6-months follow up. Dichotomous outcomes will be defined. These include the development of probable major depression (as indicated by PHQ-9 results) in participants who did not meet this criterion at baseline and remission from sub-threshold depression in those who fell into this category at baseline. Relative risk will be calculated and tested for significance. The numbers needed to treat to avoid one person developing major depression and to achieve one remission from sub-threshold depression will be calculated.

In addition to intervention group, a number of variables will be examined to see if they predict outcomes: age, gender, education level, past diagnosis of depression, past diagnosis of psychotic disorder, whether they sought help during the intervention, baseline self-help for depression self-efficacy, and whether they had experienced an adverse life event in the six months prior to the development of sub-threshold depression.

Other outcomes include coping strategies used, knowledge of depression, and self-help for depression self-efficacy. In order to determine whether any change in depression might be due to changes in coping behaviour, the coping strategies used by participants will be evaluated. Usage rates and change in usage of each strategy in each intervention group will be compared pre- and post-intervention. Change in use of each strategy will be evaluated using logistic regression expressed as odds ratios with their 95% confidence intervals. Each strategy's mean perceived helpfulness for participants using them will also be compared pre- and post-intervention between groups.

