Conducting assessments of outcomes on the web also poses several limitations. There are concerns about the equivalence in validity and reliability of web-based assessments to paper-and-pencil based assessments [73], though when this has been evaluated with depression or mental health assessments there is little evidence of differences between the two administration modes [74,75]. In addition, all outcome measures are self-rated by definition, rather than the preferred method of clinical ratings or diagnostic interviews. Self-rated assessment may be vulnerable to respondent bias [76] and other causes of depression (e.g., medication side effects, physical diseases) cannot be ruled out as would occur in a diagnostic interview, nor are co-morbid mental disorders assessed. However, the study asks participants at baseline about bereavement and history of mania or psychotic disorders. The presence of these could be used in a sensitivity analysis. We decided not to exclude individuals with these profiles from participating, because we wanted to test whether the approach is feasible and effective as a first step, so we kept exclusion criteria to a minimum.

Limited research suggests that email-based interventions are a promising method of delivering health behaviour change interventions. In contrast to website-based interventions, email-based interventions may be more convenient to participants because they do not have to take conscious action in order to receive content. These interventions have the advantage of *stickiness *[77,78], the concept that ideas and intentions are more likely to 'stick' (i.e. make an impact and be remembered) when they appear frequently in the person's environment. They are also potentially easier to implement than complex website-based interventions and hence could have better cost-effectiveness. Website-based depression interventions can be effective but require considerable user commitment and usually health professional involvement [79]. If the email-based approach used in this study proves effective, the Mood Memos intervention could be broadly disseminated and be a low-cost way of reducing the population burden of depressive symptoms.

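### The only stated rule for probable major depression is a bare count of five symptoms, so the prevention endpoint can be met without depressed mood or loss of interest

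*Protocol article*

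**What the plan says.** The Trial procedure section sorts visitors into three groups by symptom count. Entry requires "Sub-threshold depression: 2 to 4 symptoms of depression present for more than half the days or nearly every day". The excluded higher group is "Probable major depression: 5 or more symptoms of depression present for more than half the days or nearly every day". Both carry the further condition "for 2 weeks or more, with significant impact on functioning". One item has its own threshold: "except for suicidality, which is counted as a symptom if present for only several days or more". The non-depressed group is the remainder, explained by an insufficient count, duration or impact; absence of a core symptom is not among the reasons. The Participants section gives the same two-to-four count for admission.

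The symptom pool is tied to the diagnostic standard: "Depression symptoms are defined as the nine symptoms in criterion A of DSM-IV Major Depressive Episode [16] assessed with the PHQ-9". The Depression section says of the PHQ-9: "It is a self-rated questionnaire that makes probable diagnoses of mental disorders based on DSM-IV criteria".

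The Statistical analysis section then names as a dichotomous outcome "the development of probable major depression (as indicated by PHQ-9 results) in participants who did not meet this criterion at baseline", to be summarised by a relative risk and a number needed to treat. The Abstract puts prevention of major depression in the primary hypothesis beside symptom reduction. The Assessment section makes the continuous PHQ-9 score the primary outcome.

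**The concern.** The article borrows the symptom list and the threshold of five from DSM-IV criterion A, but its operational rule treats all nine symptoms as interchangeable. Criterion A also requires depressed mood or loss of interest to be among the five. If the system scores what is written, some events reported as major depression would not meet the standard the article names.

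What is at stake is the meaning of the prevention endpoint. The active emails include messages on eating, sleep and activity (Table 1). Under a bare count, a change in such symptoms alone could move a participant across the threshold and be reported as a case of major depression prevented.

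**Working it through.** **Does the screening rule carry over to the endpoint?** The Statistical analysis section refers to participants who did not meet the criterion at baseline. Table 2 shows the PHQ-9 at screening and not in the baseline package, so baseline status can only be the screening category. No second algorithm is given. Applying the screening rule at follow-up is therefore an inference, but it is the only reading the article supplies.

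**Is the core-symptom condition stated anywhere?** The Participants, Trial procedure, Depression and Statistical analysis sections contain no such condition. The one item-specific provision concerns suicidality.

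**How many symptom patterns are affected?** Inputs: nine symptoms and a threshold of five (Trial procedure); two core symptoms, taken as PHQ-9 items 1 and 2 (assumption from the invoked standard; the article does not list the items).

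- Patterns with five or more of nine: C(9,5) + C(9,6) + C(9,7) + C(9,8) + C(9,9) = 126 + 84 + 36 + 9 + 1 = 256.
- Of these, patterns with neither core symptom: C(7,5) + C(7,6) + C(7,7) = 21 + 7 + 1 = 29.
- Share: 29/256 = 11.3%. A core-symptom condition leaves 256 − 29 = 227.
- Entry rule, two to four of nine: 36 + 84 + 126 = 246 patterns, of which 21 + 35 + 35 = 91 (37.0%) have neither core symptom.

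These counts weight every pattern equally. They show what the rule permits, not how often it happens.

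**How many patterns are purely bodily?** If four items are bodily (sleep, appetite, fatigue, psychomotor; assumption), none of the 256 patterns qualifies, since five symptoms are needed. If concentration is added, C(5,5) = 1 of 256 does.

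**What happens to the relative risk?** Let f be the share of control-arm events without a core symptom, RR_c the relative risk for events with one, and RR_n the relative risk for events without. Then

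observed RR = (1 − f) × RR_c + f × RR_n.

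The article gives none of these three quantities. With assumed RR_c = 0.70 and RR_n = 1, f = 0.10 gives 0.90 × 0.70 + 0.10 = 0.73, and f = 0.20 gives 0.80 × 0.70 + 0.20 = 0.76. With RR_n also 0.70, the observed value stays at 0.70 for any f. Size and direction both depend on RR_n, which is unknown.

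**What happens to the number needed to treat?** Assume a 20% control event rate, f = 0.20, RR_c = 0.70 and RR_n = 1. Non-core events are 0.20 × 20% = 4.0% in each arm.

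- Core events: 16.0% control, 0.70 × 16.0% = 11.2% active; difference 4.8 points.
- All counted events: 20.0% control, 11.2% + 4.0% = 15.2% active; difference 4.8 points.

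The number needed to treat is 1/0.048, about 21, under both definitions.

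**Is the sample size touched?** The Sample size section gives 393 per condition for 0.2 SD, 80% power and a pre-post correlation of 0.5. With two-sided alpha 0.05 (assumed) and change-score SD √(2 × (1 − 0.5)) = 1, the calculation returns 393. Allowing for 33% dropout, 786/0.67 gives 1174, which 1200 covers. The calculation rests on a continuous outcome, so the outcome rule does not enter it.

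**The case against.** The strongest objection is that a journal article condenses item-level scoring, and that by citing the PHQ-9 and DSM-IV it imports their full algorithm. This has some force, because the core-symptom clause is in the cited standard and not in the article. But the Trial procedure section is not silent on scoring. It prints a complete-looking rule, includes an exception for one item, and says who counts as non-depressed. Someone with five non-core symptoms, the required duration and functional impact can only fall into the major-depression group.

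A second objection is that the rule is the same in both arms and the primary outcome is continuous. That stands, and it limits the point to endpoint validity; it is not a bias between arms.

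A reader might also infer stronger versions, which the article does not support:

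- **That purely somatic complaints can generate the endpoint.** At most 1 of 256 patterns fits, and only if concentration is classed as bodily.
- **That such events are beyond the emails' reach and must dilute the relative risk.** Table 1 lists active emails on sleep, eating and activity, so no treatment effect on these events cannot be presumed. No source exists for their share.
- **That the number needed to treat is distorted.** With equally frequent non-core events in both arms, it is unchanged.
- **That the missing condition lets in physical illness.** The Discussion already concedes that "other causes of depression (e.g., medication side effects, physical diseases) cannot be ruled out as would occur in a diagnostic interview", and a core-symptom condition would not rule those causes out either.

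**Conclusion.** The point holds as a defect in the definition of the dichotomous prevention endpoint. As written, incident probable major depression can be assigned with neither depressed mood nor loss of interest, while the article describes the diagnosis as DSM-IV based. In terms of patterns, 29 of 256 qualify this way. The share of actual events is unknown and could be close to zero, since duration and functional impact are also required and recruitment draws partly on depression-related sources. The effect on event rates and relative risk cannot be computed from the article.

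The conclusion rests on two assumptions: that the screening rule is the one used at follow-up, and that the invoked standard requires a core symptom. The entry rule has the same feature, but who is admitted is a debatable design choice and is not counted as an error here.

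**What to change.** Reconcile the Trial procedure, Depression and Statistical analysis sections by stating the incident outcome in full. Probable major depression at follow-up should need five or more symptoms, with the existing duration and impact conditions, of which at least one is PHQ-9 item 1 or item 2 at more than half the days or above. Report the any-five count as a sensitivity analysis.

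Leave the screening, eligibility and referral rule as it is, and report how many participants entered with neither core symptom. The outcome definition is then narrower than the screening exclusion, but the set at risk does not change: entrants have two to four symptoms, so none is a case at baseline under either definition. The report should state the difference between the two rules.

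The cost is small. The items are already collected and scoring is automated. The downside is slightly fewer events.

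### At screening, the stated help message goes with the probable major depression class, so a screenee who endorses suicidality but is classed non-depressed is turned away without it

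*Protocol article*

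**What the plan says.** All of the following is in the protocol article, under Trial procedure unless another section is named.

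- **Classes.** Sub-threshold depression is 2 to 4 counted symptoms and probable major depression is 5 or more. Both also require a duration of at least two weeks and significant impact on functioning. The third class, non-depressed, is the remainder: "not meeting criteria for sub-threshold or major depression, i.e. too few symptoms, too short duration, little or no impact on functioning".
- **Suicidality item.** A symptom normally counts from more than half the days, "except for suicidality, which is counted as a symptom if present for only several days or more". No other use of the item at screening is stated.
- **What the two ineligible classes receive.** "Those whose results indicate major depression or non-depressed will be given feedback on their score and informed that they are not eligible to participate".
- **What one of them receives as well.** "In addition, those with major depression will be encouraged to seek professional help and will be directed to a section on the website". That section lists, by country, organisations offering help or support.
- **Automation.** "Depression status is scored by the system and trial eligibility is determined immediately, based on admission criteria".
- **What follows for the sub-threshold class.** "Participants with a positive screen for sub-threshold depression will be assessed to see whether they meet further inclusion criteria". Under Participants, one of those criteria is that people "are not receiving treatment for depression from a professional (e.g., doctor, counsellor, psychologist), not including maintenance antidepressant medication for 6 months or more". None of the admission criteria concerns suicidality.

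**The concern.** The plan treats suicidality as more serious than the other symptoms, since it alone counts at the lower frequency. That extra sensitivity is used only for classification. Whether a screenee is pointed to help depends on the class, and the class depends on how many other symptoms are present, how long they have lasted and whether they impair functioning. Someone can report suicidal thoughts nearly every day and still fall in the class that is told it does not qualify and, as the rule is written, is not encouraged to seek help.

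What is at stake is the safety of people who leave the study at screening. Administration is fully automated and assessment is by self-report on the website. The article describes no clinician contact at which a missed case would be noticed.

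**Working it through.** There is no figure in the plan to reproduce. The check is to run the stated classification rule with the suicidality item positive.

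**Inputs**
- Item scores run from 0 to 3 by frequency (Depression section). The article labels only the two end points. I take 1 as several days and 2 as more than half the days, the order that the thresholds in Trial procedure imply.
- s = 1 if the suicidality item is scored 1 or more, otherwise 0.
- k = number of the other eight items scored 2 or more, so k runs from 0 to 8.
- Counted symptoms n = s + k.
- If duration and impact are both met: n of 0 or 1 is non-depressed, n of 2 to 4 is sub-threshold, n of 5 or more is probable major depression. If either is not met, the class is non-depressed whatever n is.

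**Result with suicidality endorsed (s = 1)**

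| Duration and impact | Other counted symptoms k | n = 1 + k | Class | Help message by the stated rule |
|---|---|---|---|---|
| Both met | 0 | 1 | Non-depressed | No |
| Both met | 1 to 3 | 2 to 4 | Sub-threshold | None described |
| Both met | 4 to 8 | 5 to 9 | Probable major depression | Yes |
| Either not met | 0 to 8 | 1 to 9 | Non-depressed | No |

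**Does the item have any effect of its own?** Compare s = 0 with s = 1 when duration and impact are met. At k = 1 the class moves from non-depressed (n = 1) to sub-threshold (n = 2). At k = 4 it moves from sub-threshold (n = 4) to probable major depression (n = 5), which brings the message. At every other k the class is unchanged. So the item can tip someone into the class that gets the message when exactly four other symptoms count, but it never produces the message by itself. Scores of 1, 2 and 3 on it are treated alike.

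**Two illustrations, which are not frequencies**
- Suicidality scored 3 and two other items scored 1 each, duration and impact met: total 3 + 1 + 1 = 5, k = 0, n = 1, non-depressed, no message.
- All nine symptoms counted (n = 9) with little or no reported impact: non-depressed, no message.

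**Is the contrast stated or merely unsaid?** The sentence on score feedback and ineligibility names both ineligible classes. The next sentence opens with words of addition and names only one of them. For the non-depressed class, then, the article sets out what is given, and the help message is not part of it. For the sub-threshold class the article only describes the route to enrolment and says nothing either way.

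**The case against.** The strongest objection is that this is a condensed article. The help sentence does not contain the word only, and the paragraph is about eligibility and feedback rather than suicide-risk handling. Such handling is often left to the full protocol and the ethics submission, and the Design section reports ethics approval. The wording of the score feedback is not shown and could include advice on help. The contact page belongs to the website the screenee is already using, and nothing says that access to it is restricted. Nothing in the text is contradictory.

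These points limit how certain any harm is, and they rule out some stronger readings. A reader might infer that suicidal screenees are given no help information at all, or that the trial has no suicide-risk procedure. The article supports neither. They do not remove the point itself, because the article does state who gets the message and on what trigger, and that trigger leaves out the people described above.

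A reader might also infer that enrolling sub-threshold people who endorse suicidality is an error. That does not follow. The plan deliberately counts the item toward eligibility, and the Discussion explains that exclusions were kept to a minimum. For this group the absence of a described message is silence in a condensed text, so it supports only a secondary suggestion.

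Nor can one say that the non-depressed screenees are untreated. The no-treatment criterion applies to those who go on to enrolment, and the article describes that check only after a positive sub-threshold screen.

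One further part of the objection stands. For people who will be enrolled, a prompt to seek professional help is not entirely free, as set out under the fix.

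**Conclusion.** The point holds for the non-depressed class. By the rule as stated, a screenee scoring 1 or more on the suicidality item is told of ineligibility without the help message whenever no other symptom counts, or duration or impact is not met. With the item endorsed, the message requires k of at least 4 together with duration and impact.

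The number affected cannot be computed, because the article gives no rate of positive suicidality answers among screenees. The conclusion assumes that the system follows the rule as written, and that neither the unseen feedback text nor the full protocol already supplies the message.

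This is a change that should be made on safety grounds, with medium confidence because of those unseen documents. A reader might take it to weaken the trial's results. It does not: the people concerned are never randomised, and the estimand, the stated power calculation and the analysis method are untouched.

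**What to change.** **Main change.** Keep the present trigger for probable major depression. Add a second one: show the existing help message, with its country-specific contacts, to any ineligible non-depressed screenee scoring 1 or more on the PHQ-9 suicidality item. If the full protocol already does this, no change is needed beyond a sentence in the article. The cost is one condition in the automated script and reuse of an existing page. These people do not enter the trial, so the randomised sample is unaffected.

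**Secondary suggestion.** Consider showing the same message, before randomisation, to sub-threshold screenees who endorse the item, if no such step exists. Given before allocation, it cannot differ by arm and so cannot bias the comparison. It may raise professional help-seeking in both arms, however. The plan already records help-seeking as a possible confounder (Other) and examines it as a predictor of outcome (Statistical analysis). More of it in both arms could slightly dilute a contrast planned at 0.2 standard deviations (Sample size). The documents give no basis for sizing that dilution. The sponsor should weigh it against the safety gain.
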